## Introduction

LBP is a common complaint in the general population, and its incidence is about five times higher in patients with LDD and Modic endplate changes [1, 2]. The link between these findings and the isolation of low virulence pathogens in LIVD has already been described in several studies, generating a lot of interest in the topic and promoting the bacterial hypothesis of LDD [3–14].

Albert et al. reported 46% of positive cultures for anaerobes in 61 patients undergoing lumbar discectomy, of which 80% had Modic type 1 changes [15]. Other studies corroborate these findings, with high identification rates for *Cutibacterium acnes*, an anaerobic and aerotolerant pathogen that is bacillus-shaped, stained by the Gram method, pleomorphic, non-spore-forming, and a biofilm producer [11, 16–20]. Rollason et al. isolated strains of this bacterium from the LIVD of 64 patients, revealing the presence of genotypic profiles distinct from those found in the skin, suggesting that specific variants would be related to LBP [21].

Other authors believe that the presence of this pathogen in the LIVD of asymptomatic patients is due to contamination of the specimens during sampling and/or sample treatment in the laboratory environment. Carricajo et al. found positive cultures for *C*. *acnes* in only 3.4% of the discs from 54 patients, defending the possibility of contamination [22]. Rigal et al. also analyzed LIVD from 313 patients who underwent video-assisted retroperitoneal discectomy, with positive cultures for only six patients [23].

These marked divergences in microbiological results cast doubt on the bacterial hypothesis of LDD and, consequently, raise questions about the possibility of anaerobic pathogens acting as triggers or amplifiers of LBP. Urquhart et al. conducted a systematic review of the literature on the subject and concluded that there is evidence correlating the *C*. *acnes* isolation with Modic type 1 changes and LBP, but there is a lack of studies producing substantial and irrefutable evidence [24].

Despite the fact that considerable effort has already been expended in determining the presence of *C*. *acnes* in LIVD, there are still no standard isolation protocols for this pathogen from this clinical specimen. Furthermore, prior to the preparation of this manuscript, studies have shown no consistency in the collection and analysis techniques used, making comparison and reproducibility of results difficult.

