## Statistical planning

### Sample size calculation

Considering the main outcome proposed, the identification of disc colonization by *C*. *acnes*, the minimum sample size (*n*) for the population of interest will be 96 participants, according to the calculation described by Medronho et al., [59] using a confidence interval of 95% and a maximum margin of error of 10%.

The ideal sample size for analysis of secondary outcomes will depend on the incidence of the main outcome. If it is too low, an increase in the number of patients included will be performed with the inclusion of more blocks of participants. In order to have a more accurate dimension, the sample size calculation will be revised as soon as we reach half of the initially planned sample size.

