### Statistical analysis methodology

The database will be analyzed using the SPSS software, version 22.0, and R software, version 4.0.2. Descriptive analysis will be performed by charts and descriptive statistics. The inferential analysis will consider a maximum significance level of 5%. The chi-square test or Fisher’s exact test will be used for inferential analysis of the distributions of categorical variables. The odds ratio (OR) will be the measure used to estimate risk. The OR’s significance will be evaluated by the OR’s asymptotic confidence interval. The hypothesis of normality will be verified by the Kolmogorov–Smirnov and Shapiro–Wilk tests. Student’s t-test or Mann-Whitney test will be used in the comparison of the two independent groups. More than two independent groups will be compared by the ANOVA or by the Kruskal–Wallis test. Two repeated measures in different assessments will be compared by the paired Student’s t-test or by the Wilcoxon’s signed-rank test. More than two repeated measures will be compared by the ANOVA for repeated measures, or by the Friedman’s test.

The identification of an optimal cutoff point for the marker associated with an outcome will be established through the analysis of the receiver operating characteristic (ROC) curve. The performance will be evaluated by the area under the ROC curve (AUC), and the significance of the AUC will be evaluated by the test that judges the null hypothesis that AUC is equal to 0.5. In addition to the significance test, the asymptotic confidence interval for the AUC will be obtained.

Analysis of the association between two quantitative variables will be visualized by scatter plots and quantified by the Pearson correlation coefficient, in the case of normal distributions, or by the Spearman’s correlation coefficient, if normal distribution is not verified in at least one of the variables. The significance of the correlation coefficient will be evaluated by the correlation coefficient test.

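### Two significance rules apply to the same 2×2 table with no stated precedence, and in sparse tables the odds ratio's asymptotic interval can fail or contradict Fisher's test

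*Protocol article*

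**What the plan says.** All references are to the protocol article.

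- Statistical analysis methodology, on tests: "The chi-square test or Fisher’s exact test will be used for inferential analysis of the distributions of categorical variables".
- Same section, on the effect measure: "The odds ratio (OR) will be the measure used to estimate risk".
- Same section, on judging that measure: "The OR’s significance will be evaluated by the OR’s asymptotic confidence interval".
- Same section, on alpha: "The inferential analysis will consider a maximum significance level of 5" per cent. Sidedness is not stated; two-sided is assumed below.
- Sample size calculation: "the minimum sample size (*n*) for the population of interest will be 96 participants", obtained "using a confidence interval of 95% and a maximum margin of error of 10" per cent. On low incidence: "If it is too low, an increase in the number of patients included will be performed". No threshold or target is given.
- Introduction: one series "found positive cultures for *C*. *acnes* in only 3.4% of the discs from 54 patients", another had 6 positive among 313 patients, and a third reported 46% positive for anaerobes, 80% of them with Modic type 1 changes.
- The objectives and the Modic changes section cross colonization (yes/no) with Modic type 1 (yes/no), so this 2×2 table will be built.
- The last paragraph of the statistical section fits logistic models for colonization by maximum likelihood with forward Wald selection.

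**The concern.** One table can receive two verdicts: a p-value from the chi-square or Fisher test, and a judgement on whether the OR's interval excludes 1. In large tables the two nearly always agree. In sparse ones they need not, because the usual asymptotic interval takes its standard error from the reciprocals of the observed cells. An empty cell makes the OR zero or infinite and the standard error undefined.

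The protocol's own background makes sparse tables a realistic prospect. If they occur, the report on Modic type 1 changes could show a significant Fisher test beside an OR that is not significant or has no interval. The analyst would then choose between them after seeing the data.

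**Working it through.** **Planned size.** n = 1.96² × 0.5 × 0.5 / 0.10² = 96.04, which reproduces 96 (the 0.5 is implied, not stated).

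**Expected colonized among 96.** 6/313 = 1.9% gives 1.8; 3.4% gives 3.3; 46% gives 44.2. The 3.4% is per disc, so applying it to patients is an assumption.

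**Interval checked.** Woolf/Wald: exp(log OR ± 1.96 × √(1/a + 1/b + 1/c + 1/d)). The protocol names neither a variant nor a correction.

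**Single tables, 3 colonized and 93 not.**

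- 3/3 versus 20/93. Fisher p = C(23,3)/C(96,3) = 1771/142880 = 0.012. One cell is 0, so there is no interval. With 0.5 added to each cell, OR = (3.5 × 73.5)/(0.5 × 20.5) = 25.1, interval 1.25 to 506.
- 3/3 versus 30/93. Fisher p = C(33,3)/C(96,3) = 5456/142880 = 0.038. There is no interval; with 0.5 added it is 0.73 to 291, which includes 1.
- 2/3 versus 12/93, the reverse conflict. OR = (2 × 81)/(1 × 12) = 13.5; SE = √(1/2 + 1 + 1/12 + 1/81) = 1.263; interval 1.14 to 161, which excludes 1. Fisher p = [C(14,2) × 82 + C(14,3)]/142880 = 7826/142880 = 0.055. Of the 184 tables of this size without an empty cell, 10 conflict in this direction.

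**Power by exact enumeration.** N = 96, all tables weighted by two binomials, two-sided 5%. The 80% among colonized follows the series cited in the Introduction; every other Modic rate is an assumption. The fourth column counts zero-cell tables as not declarable. The last adds 0.5 to zero-cell tables only.

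| Colonized | Modic 1: colonized vs not | P(empty cell) | Fisher | Interval, uncorrected | Interval, 0.5 if empty |
|---|---|---|---|---|---|
| 3 | 80% vs 20% | 52% | 52% | 3% | 49% |
| 5 | 80% vs 20% | 33% | 79% | 50% | 82% |
| 10 | 80% vs 20% | 11% | 97% | 87% | 98% |
| 10 | 90% vs 20% | 35% | 99.8% | 65% | 99.9% |
| 3 | 80% vs 30% | 52% | 46% | 0% | 8% |
| 5 | 90% vs 40% | 59% | 56% | 1% | 17% |
| 44 | 80% vs 30% | 0% | 99.9% | 99.9% | 99.9% |

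The empty-cell column follows directly; for example 0.8³ + 0.2³ = 0.52, and 0.9¹⁰ = 0.35. With 10 colonized, raising the true rate from 80% to 90% against 20% lowers the uncorrected interval's power from 87% to 65%, because empty cells become more frequent.

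**Logistic route.** Maximum likelihood on 3/3 versus 20/93 gives coefficient 22.7, standard error 15334 and Wald p = 0.999. A Wald criterion therefore fails on the same data.

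**Does an exact interval agree with Fisher?** For 3/3 versus 30/93, P(A = 3 | ψ) = 5456ψ³/(39711 + 64449ψ + 33264ψ² + 5456ψ³).

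- The central exact interval sets this to 0.025, giving ψ = 0.81. Its range of 0.81 to infinity includes 1 although p = 0.038.
- Inverting the two-sided Fisher test sets it to 0.05, giving ψ = 1.15. Its range of 1.15 to infinity agrees with the p-value.

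**The case against.** Several points on the other side carry weight.

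- **Fisher is already named.** A reader might infer that the strongest associations could never be declared. The text does not support that: the same section assigns categorical tables to the chi-square or Fisher test. What stands is the missing precedence.
- **Zero cells scored as failures.** The protocol states no such rule, and most of the loss comes from it. Adding 0.5 closes the gap in the 80% versus 20% and 90% versus 20% rows. It does not close it at 80% versus 30% with 3 colonized (46% versus 8%) or at 90% versus 40% with 5 (56% versus 17%).
- **Asymptotic need not mean Woolf/Wald.** Score and profile-likelihood intervals are also asymptotic and keep a usable limit with an empty cell. So non-existence belongs to the usual reading, not to every reading of the sentence. The protocol does not choose, and disagreement with Fisher would need settling under any choice.
- **Detail for an analysis plan.** A zero-cell convention alone could be left there. Here the protocol fixes the criterion, so a later plan would have to qualify that sentence.
- **The sample may be enlarged.** This mitigates only in part, since no threshold is given. At N = 120 with 10 colonized and 90% versus 20%, power is still 99.8% versus 65%. What helps is more colonized patients.
- **An empty cell is not proof of a strong effect.** With 3 colonized and equal 30% rates it occurs in 0.3³ + 0.7³ = 37% of tables.

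**Conclusion.** The point holds as an unresolved conflict between two stated rules, one of which fails or becomes unreliable in sparse tables. Under the uncorrected reading, with zero-cell tables not declarable, the gap reaches 35 percentage points with 10 colonized (90% versus 20%) and 49 with 3 colonized (80% versus 20%). With a 0.5 correction it ranges from practically nothing to about 38 points in the scenarios tried.

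These sizes rest on the assumed Modic rates, on applying low cited positivity rates to this study, and on the Woolf/Wald reading. At 44 colonized (46%) the two rules differ by at most one percentage point in the alternatives tried. Only secondary associations at low colonization counts are affected; the incidence estimate is not. It should be changed because the remedy is cheap, but it does not threaten the study's main result.

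**What to change.** Replace the sentence on the OR's significance with:

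*When any expected count is below 5 or any cell is empty, significance is taken from Fisher's exact test and the OR is reported with the exact 95% interval obtained by inverting that same two-sided test, so that interval and p-value agree; otherwise the asymptotic interval is used.*

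A central exact conditional interval should not be substituted, because it can contradict the two-sided Fisher p-value, as 3/3 versus 30/93 shows.

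In the logistic models for colonization, use Firth's penalised likelihood with profile-likelihood intervals where separation or sparse cells occur.

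The cost is wording, plus slightly wider intervals in some tables. With an empty cell the exact interval has an infinite upper limit (or a lower limit of zero), which should be reported as such. R, already named in the protocol, can do both.

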### Patient and public involvement

Participant eligibility will be evaluated by the study researchers through a clinical interview and imaging exams evaluation, according to the participants’ interest and availability to participate in the study. If the patient agrees to take part in the study, the predetermined selection criteria will be used to evaluate them. The researchers will explain the details of the study and conduct a joint reading of the ICF. Questions about the study objectives, risks and benefits, stages, and research confidentiality will be answered. A patient will only participate upon signing the ICF at this stage of the research. A copy of this document will be given to the participant, another to the responsible researcher, and a third will be attached to the medical record. After signing the consent form, the patient will undergo an evaluation for demographic and clinical data collection and the forms developed for this purpose will be completed. If the patient is unable to read and sign the written consent form, researchers will verbally explain the study details and the patient will orally provide consent in the presence of a witness who will sign the consent form. The recruitment of participants will take place over a 6-month period, until 120 individuals are included, aiming at a minimum number of 96 collections.

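### The t-test and ANOVA named for secondary group comparisons are, by convention, equal-variance tests, and the colonized and non-colonized groups may differ greatly in size; naming the Welch forms would protect the 5% level at little cost

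*Protocol article*

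**What the plan says.** All references are to the Protocol article.

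- **Tests.** Statistical analysis methodology states: "Student’s t-test or Mann-Whitney test will be used in the comparison of the two independent groups". More than two independent groups are to be compared by ANOVA or the Kruskal–Wallis test. The section sets a maximum significance level of 5% and does not say whether tests are two-sided.
- **Check before testing.** "The hypothesis of normality will be verified by the Kolmogorov–Smirnov and Shapiro–Wilk tests". For these group comparisons no variance check and no unequal-variance form is named. The later sentence on verifying model assumptions concerns the regression models.
- **Groups.** Secondary outcomes and Modic changes use groups defined by presence or absence of colonization. For quality of life these are further divided by Modic status.
- **Size.** In Sample size calculation, "the minimum sample size (*n*) for the population of interest will be 96 participants", for a 95% confidence interval and a margin of error of 10%. No expected colonization rate is given. If incidence proves too low for the secondary outcomes, more participants are to be added.
- **Background rates.** The Introduction cites 46% positive cultures for anaerobes in 61 patients, 3.4% of the discs from 54 patients, and a series of 313 patients "with positive cultures for only six patients".

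**The concern.** Student's t-test estimates one common variance from both groups. If the true variances differ, its standard error is wrong unless the groups are about equal in size. The larger group dominates the pooled variance, while the smaller group contributes most of the uncertainty in the difference. If the smaller group is the more variable, the standard error is too small and false positives exceed 5%. If the smaller group is the less variable, the standard error is too large and power is lost. One-way ANOVA makes the same equal-variance assumption. A normality check detects neither problem.

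The comparisons exposed are the secondary ones on quantitative variables between culture-defined groups: pain, disability, quality of life and molecular measures. Recruiting more patients when incidence is low raises the total but leaves the proportion colonized where it was, and the error depends mainly on that proportion.

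**Working it through.** **1. The plan's own figure.** For a single proportion, n = z²·p(1−p)/d². With z = 1.96, d = 0.10 and p = 0.5 (implied, not stated), n = 3.8415 × 0.25 / 0.01 = 96.04. This reproduces 96. The recruitment target of 120 agrees with 96/(1 − 0.20) = 120; the 20% loss is implied, not stated. So 96 is sized for the precision of one proportion and does not address a two-group comparison.

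**2. Possible splits of 96 at the cited rates.**
- 6/313 = 1.9%: 96 × 0.019 = 1.8, about 2 v 94
- 3.4%: 96 × 0.034 = 3.3, about 3 v 93
- 46%: 96 × 0.46 = 44.2, about 44 v 52

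The 3.4% is per disc and the 46% covers all anaerobes, so these are rough guides only. Splits at 5%, 10%, 20% and 30% are added below as assumptions.

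**3. Large-sample approximation.** Let r be the ratio of the colonized SD to the non-colonized SD, and set the latter to 1.
- True variance of the difference: V = r²/n₁ + 1/n₂
- Variance the pooled test expects to use: P = [(n₁−1)r² + (n₂−1)]/(N−2) × (1/n₁ + 1/n₂)
- Actual two-sided error: 2[1 − Φ(1.96·√(P/V))]

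For 10 v 86:
- r = 2: V = 0.4 + 0.0116 = 0.4116; P = (36 + 85)/94 × 0.1116 = 0.1437; √(P/V) = 0.591; error ≈ 0.247
- r = 0.5: V = 0.025 + 0.0116 = 0.0366; P = (2.25 + 85)/94 × 0.1116 = 0.1036; √(P/V) = 1.682; error ≈ 0.001

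For large N with a proportion p colonized, P/V tends to (p·r² + 1 − p)/((1 − p)r² + p), in which N does not appear. At p = 0.10 and r = 2 this is 1.3/3.7 = 0.351, giving an error of about 0.245. Adding patients at the same incidence therefore does not remove the problem.

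**4. Simulation.** Normal data, equal means, N = 96, two-sided 5% (assumed); 100,000 runs per cell for the two t-tests. The SD ratios are assumptions, because the protocol gives no SD.

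| Split | Student, r = 0.5 | r = 1 | r = 1.5 | r = 2 | Welch, range over r = 0.5 to 2 |
|---|---|---|---|---|---|
| 3 v 93 | 0.03% | 5.0% | 18.0% | 30.3% | 6.0–7.8% |
| 5 v 91 | 0.05% | 5.0% | 17.2% | 28.6% | 5.3–5.8% |
| 10 v 86 | 0.1% | 4.8% | 15.5% | 24.4% | 5.0–5.3% |
| 19 v 77 | 0.5% | 5.0% | 12.4% | 18.3% | 5.0–5.1% |
| 29 v 67 | 1.3% | 5.0% | 9.2% | 12.7% | 4.9–5.0% |
| 44 v 52 | 4.0% | 4.9% | 5.8% | 6.3% | 4.9–5.0% |
| 48 v 48 | 5.1% | 5.0% | 5.0% | 5.2% | 5.0–5.1% |

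The 2 v 94 split was not simulated, and neither was Welch's ANOVA.

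**5. The named alternative.** Mann-Whitney under the same conditions (20,000 runs, r = 2) rejects 15.3% at 3 v 93, 12.4% at 10 v 86 and 10.9% at 19 v 77. At r = 0.5 it rejects 0.7% at 10 v 86. It is less affected than Student's test but is not a remedy.

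**The case against.** The strongest reply is that the protocol never says pooled or equal variances. It names software, SPSS and R, that can report the unequal-variance form, and a condensed article may leave the variance form to an analysis plan that is not shown. This stands in part: the equal-variance form is an inference from the test's name. It is the ordinary meaning of that name, however, so the point concerns a method that is stated. A reader might infer that the plan rules out Welch's test; the text does not say so.

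A reader might also infer that the groups will probably be very unequal. The documents do not support that. The cited rates reach 46%, the figure of 96 implies p = 0.5, and the culture methods are designed to improve recovery. At 44 v 52 the error is at most 6.3% for the ratios examined. Very unequal groups are possible, not established.

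A third inference would be that colonized discs are the more variable group, so that false positives are to be expected. Nothing in the documents links colonization to the spread of pain, disability, quality-of-life or molecular measures. Inflation needs unequal groups, unequal spread, and the larger spread in the smaller group, all together. With the spread reversed the test is conservative; with equal spread it is nominal at every split.

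Finally, the simulation applies the t-test to exactly normal data, whereas the plan also offers a rank test, and where that is used naming Welch changes nothing. That is correct, and it limits what the fix can achieve.

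**Conclusion.** The point holds as a minor, conditional one. The named t-test and ANOVA, in their conventional form, keep the stated 5% level only if the spreads are equal or the groups are of similar size. The protocol supports neither condition with a figure, and the group sizes cannot be known until cultures are read. At an assumed 10 v 86, the actual level is about 15% or 24% for a colonized SD of 1.5 or 2 times the other, and about 0.1% for half. At 44 v 52 it is 4.0% to 6.3%.

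These figures rest on assumed SD ratios, normal data, N = 96 and two-sided testing. They show what could happen and do not predict what will. The primary outcome is a single proportion and is unaffected.

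**What to change.** In Statistical analysis methodology, replace Student's t-test for two independent groups with Welch's unequal-variance t-test, and name Welch's ANOVA for more than two independent groups. The ANOVA change follows from the same equal-variance assumption and was not computed separately. Add a sentence that comparisons resting on only a few colonized patients will be treated as descriptive, since Welch's test itself rejects about 6% to 8% at 3 v 93. Do not offer Mann-Whitney as protection against unequal spread.

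The cost is a small edit to the text, with no change to data collection, sample size or software. The downside is slightly less power if the variances are in fact equal and the colonized group is small. The change works in both directions of the SD ratio, so it requires no guess about which group is the more variable. It is best made before the culture results are linked to the secondary outcomes.

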### Withdrawal of a study participant

A participant will be removed from the study in cases of ICF withdrawal, death, recruitment failure identification, loss of post-surgical follow-up, or the presentation of clinical symptoms of infection, intense pain, fever without other infectious *foci*, increased erythrocyte sedimentation rate and/or C-reactive protein, leukocytosis, imaging tests compatible with spondylodiscitis, or any other condition that leads to blinding interruption.

The reason and circumstances of each participant’s withdrawal from the study will be detailed. The data gathered until the patient is withdrawn from the study will be included in the final analysis.

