### Questionnaires

Questionnaires on pain (VNS), functionality (ODI), and quality of life (EQ-5D) will be given at recruitment as well as at 1, 3, and 6 months postoperatively. A professional who is not involved in the study will collect all questionaires. Follow-up clinical visits will be carried out at 1, 3, and 6 months postoperatively, with acceptance deviation of 7, 14, and 21 days, respectively.

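### Repeated-measures ANOVA and Friedman's test shut the observed visits of post-surgical withdrawals out of the four-visit comparison of pain, function and quality of life, although the withdrawal rule says their data will be analysed

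*Protocol article*

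**What the plan says.** Four places in the protocol article bear on this.

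- **Withdrawal of a study participant.** The reasons for removal include "loss of post-surgical follow-up, or the presentation of clinical symptoms of infection, intense pain, fever without other infectious" foci, as well as consent withdrawal and death. The section closes with the rule "The data gathered until the patient is withdrawn from the study will be included in the final analysis".
- **Questionnaires.** The pain, function and quality-of-life instruments "will be given at recruitment as well as at 1, 3, and 6 months postoperatively", which makes four assessments.
- **Statistical analysis methodology, repeated measures.** "More than two repeated measures will be compared by the ANOVA for repeated measures", with Friedman's test as the alternative. For two assessments: "Two repeated measures in different assessments will be compared by the paired Student’s t-test or by the Wilcoxon’s signed-rank test".
- **Statistical analysis methodology, groups.** "Student’s t-test or Mann-Whitney test will be used in the comparison of the two independent groups".

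No other method is named for comparing more than two repeated measures.

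**The concern.** Classical repeated-measures ANOVA and Friedman's test need a full row of visits for each participant. Someone who attends recruitment, month 1 and month 3 and then leaves supplies three of four values, and the four-visit comparison uses none of them. For that comparison, the named methods cannot deliver what the withdrawal rule promises.

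The loss need not be random. Pain is a secondary outcome and intense pain is a reason for removal. Dropping those participants takes some of the worst courses out of every visit, including visits at which they were measured. The estimated course over time, and any contrast of colonized with non-colonized participants drawn from the same complete cases, can then be biased as well as less precise.

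**Working it through.** **1. The plan's own figures.** Sample size for one proportion: 1.96² × 0.5 × 0.5 / 0.10² = 96.04, which reproduces the stated 96 (the 0.5 is the usual worst case and is not stated). The protocol recruits "until 120 individuals are included, aiming at a minimum number of 96 collections": 96 / 0.80 = 120. That 20% is loss between inclusion and specimen collection. It is not a post-surgical withdrawal rate, and the protocol gives none.

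**2. The mechanism.** In a test data set of 20 subjects with four visits, the last visit was deleted for 4. A standard repeated-measures ANOVA routine rejected the data as unbalanced. Friedman's test returned no value. With omission switched on, it gave exactly the result for the 16 complete subjects (2.775, p = 0.428).

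**3. How much is set aside.** Assume w participants withdraw, spread evenly over the three follow-up intervals. They have 1, 2 or 3 observed visits, 2 on average, so 2w observed visits per instrument are dropped.

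| Participants | Assumed withdrawal | Kept in four-visit test | Observed visits dropped |
|---|---|---|---|
| 96 | 5% (w = 5) | 91 | 10 |
| 96 | 10% (w = 10) | 86 | 20 |
| 96 | 20% (w = 19) | 77 | 38 |
| 120 | 20% (w = 24) | 96 | 48 |

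In the last row, a paired test of baseline against month 1 still keeps 96 + 24 × 2/3 = 112 participants, and baseline against month 3 keeps 96 + 24/3 = 104.

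**4. Effect on change over time.** Assume mean VNS 7 at baseline and 4 afterwards, SD 2.5 and correlation 0.5 between visits, with the fraction d having the highest month-1 pain leaving after that visit. Among those who stay, the month-1 mean falls by 2.5 × φ(z) / (1 − d), where z is the upper-d normal quantile. The baseline mean falls by half of that.

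- d = 20%: 2.5 × 0.280 / 0.80 = 0.875, so the month-1 change is −3 − 0.44 = −3.44 (simulated −3.43).
- d = 10%: 2.5 × 0.1755 / 0.90 = 0.487, giving −3.24 (simulated −3.24).
- d = 5%: 2.5 × 0.103 / 0.95 = 0.271, giving −3.14 (simulated −3.12).

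Improvement at month 1 is overstated by 0.1 to 0.4 points. The month-6 change is essentially unbiased here, because with equal correlations the shifts at baseline and month 6 cancel.

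**5. Effect on the group difference.** Assumed inputs:

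- 96 patients, 44 colonized (46%, the culture-positive share of one earlier study cited in the Introduction);
- means, SD and correlation as in step 4 for the non-colonized;
- colonized 1.5 points higher at months 1, 3 and 6, with no difference at baseline;
- exit after a month-1 or month-3 VNS above 7.5, so that about 22% leave.

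| Estimate of the true 1.5 | Month 1 | Month 3 | Month 6 |
|---|---|---|---|
| Complete cases | 0.92 | 0.94 | 1.12 |
| Per-visit two-group test | 1.49 | 1.27 | 1.12 |
| Likelihood, all observed visits | 1.49 | 1.51 | 1.49 |

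Repeat runs agree to within a few hundredths. Complete cases also show a spurious baseline difference of nearly −0.4. With the exit threshold at 8.5 (about 12% leaving), complete cases give about 1.1, 1.1 and 1.2.

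**6. Precision if 20% leave at random after month 1 or 3.** The SE of the month-1 difference on everyone observed is 2.5 × √(1/44 + 1/52) = 0.51. On complete cases it is 0.51 / √0.80 = 0.57.

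**The case against.** The strongest reply is that the two statements can both be true. The withdrawal rule does not say that every visit enters every test. Descriptive statistics, paired tests, per-visit t or Mann-Whitney tests and the month-1 30% criterion all work without four visits. A reader might infer that withdrawn participants lose all their pain, function and quality-of-life data. The document does not support that: the loss is confined to the comparison of more than two repeated measures, and someone who leaves after month 6 loses nothing. Nor is the primary outcome touched, since colonization is determined from specimens taken at surgery.

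A reader might also infer that the plan's colonized versus non-colonized contrast is cut by about a third at every visit. That is the complete-case result. The repeated-measures sentence names no group factor, and two-group comparisons go to the t or Mann-Whitney test. At month 1 that test is unbiased in the illustration and keeps the SE of 0.51. At month 6 it is as biased as complete cases, but because later visits are absent, not because collected data were discarded. That part is not evidence against the withdrawal rule.

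Further, the rate, SD, correlation, effect and exit rule are all assumed. Exit depends only on an observed score, which favours the likelihood method by construction.

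Finally, handling of missing visits may sit in a fuller document, and its absence here is no finding. What remains does not depend on it: the article names a method for more than two repeated measures, and without some added device that method cannot use the data the article says it will use.

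**Conclusion.** The point holds in a limited form. For VNS, ODI and EQ-5D across four visits, the named methods use only complete cases, so the observed visits of anyone leaving between surgery and month 6 are left out of that comparison, contrary to the intent of the withdrawal rule. Because intense pain and infection signs lead to removal, the omission may be informative.

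Its size is unknown, as no post-surgical withdrawal rate is given. At an assumed 5% to 20% of 96 patients, 10 to 38 observed visits per instrument drop out. Under the assumed pain-driven exits, month-1 improvement is overstated by 0.1 to 0.4 points, and a complete-case group difference of 1.5 shrinks to between 0.9 and 1.1. It should be changed, but it concerns secondary outcomes only.

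**What to change.** In Statistical analysis methodology, make the longitudinal analysis of VNS, ODI and EQ-5D a linear mixed model for repeated measures. Use visit, colonization and visit-by-colonization as fixed effects and an unstructured covariance, fitted by REML to all observed visits. Withdrawn participants then contribute every visit up to withdrawal, and the interaction tests directly whether the two groups follow different courses. Report the number contributing at each visit.

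The cost is a change of wording; both software packages named in the plan can fit the model. It has two downsides: it assumes that missingness depends on observed values, and it assumes approximate normality for bounded scores. A rank-based or complete-case analysis can therefore be kept as a sensitivity analysis.
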